#### *Analysis plan*

Data will be retrieved from the online survey platform. De-identified datasets and codebook will be stored for statistical analysis. The syphilis testing proportion in each arm (control, standard self-testing, and lottery incentivized self-testing) will be assessed using an intention-to-treat analysis during the follow-up period, excluding confirmatory tests after a reactive self-test.

The effects of the intervention will be measured by comparing the differences in proportions of men who take syphilis testing during two rounds of follow up by using generalized estimating equation (GEE) model. We will use the chi-square test to compare differences in the proportion of linkage to syphilis clinical care, have HIV and other STI (chlamydia, gonorrhea) testing performed, and have condomless sex events with different partners within six months of randomization across three groups and use post-host test to check the significance of differences between each of the two groups.

We will estimate the total and incremental unit costs for each arm. All costs will be identified as start-up costs, fixed costs and variable costs. Start-up costs are incurred during the process of creating this study (e.g. survey platform coordination). Fixed costs are costs that do not change with an increase or decrease in the number of people served during the trial period (e.g. administration, office equipment). Variable costs are expenses that vary with the number of participants served (e.g. recruitment, supplies, postage fee). We will first calculate the total cost for each group, then divided these costs by the number of men tested and the number of newly identified syphilis cases detected in each study arm to obtain the incremental unit costs. In addition, we will build a decision tree model using a healthcare provider perspective to estimate the incremental cost for per additional person tested and case identified for each intervention will be calculated. Univariate, multivariate and probabilistic sensitivity analyses will be conducted to test the robustness of our results.

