**Background**

Men who have sex with men (MSM) are disproportionately affected by syphilis worldwide. The WHO estimates the prevalence of syphilis among MSM is 5% or more in at least 42 countries (15 countries in Asia including China with a prevalence of 5.1%), 10% or more in 20 countries ( 6 countries in Central America and 5 countries in South America ) and more than 20% in eight countries including 3 Pacific Island countries and 2 South American countries [[1](#_ENREF_1)]. Expanding access to syphilis testing so that individuals receive a timely diagnosis and treatment, plays a key role in the control of syphilis transmission [[2](#_ENREF_2)]. Evidence shows that for men who are HIV positive and/or MSM, screening every three months (compared with screening every six or twelve months) is associated with increased detection rates at various stages of syphilis infection [[3-7](#_ENREF_3)]. Increases in syphilis screening frequency are associated with increased detection of early asymptomatic syphilis with relative falls in secondary syphilis for both HIV-positive and HIV-negative MSM in Australia, suggesting a possible interruption of syphilis progression [[8](#_ENREF_8)].

However, given the cost of the tests, anticipated stigma, and the infrastructure requirements, syphilis testing rates are generally low, especially in resource-limited settings. Previous research shows that only 30% of Chinese MSM have ever tested for syphilis [[9](#_ENREF_9)]. Whilst traditional testing for syphilis is health facility-based, recent advances in testing techniques, including dried blood spots, point-of-care testing, and self-testing, have enabled decentralized testing strategies [[10](#_ENREF_10)]. Among these innovations, self-testing offers a great potential to expand syphilis testing among hard-to-reach populations due to its convenience, confidentiality, and relatively high sensitivity and specificity [[11](#_ENREF_11), [12](#_ENREF_12)]. Evidence from HIV self-testing studies have demonstrated its effectiveness in increasing HIV testing frequency among MSM in a variety of settings [[13-15](#_ENREF_13)]. In view of this, WHO subsequently released guidelines recommending HIV self-testing [[16](#_ENREF_16)].

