**Study design**

This is a non-blinded, open-label, parallel RCT with individuals randomized in a 1:1:1 ratio to three study arms: control arm (standard of care); standard syphilis self-testing arm; and lottery incentivized syphilis self-testing arm. Control arm participants will receive information on self-referral pathways for free facility-based syphilis testing. Both self-testing arms will be offered to access syphilis self-test kits for free at monthly intervals. Participants in each arm will be followed-up for six months (Figure 1). The study hypothesis had been tested in a pilot study, completed in October 2019, which examined the feasibility of implementing the self-testing and crowdsourced lottery incentivized syphilis self-testing model among 145 Chinese MSM. The pilot study showed that both standard self-testing arm (0.74) and lottery incentivized arm (0.70) increased the frequency of syphilis testing more than the control arm (0.36). Preliminary data from this pilot study was used to inform this definitive trial design. Preliminary results are available on the supplement materials. The definitive trial, outlined in the current trial protocol, has begun in December 2019, and is expected to be completed in July 2020.

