**Surveys**

**Baseline:** All participants complete a self-administered survey on an online survey platform (Wen Juan Xing, https://www.wjx.cn) at enrolment. The baseline survey includes questions on socio-demographic characteristics, sexual behaviors, past HIV/syphilis testing and treatment, and attitude towards syphilis self-testing.

**Follow-up surveys:** Participants in the three arms of the study will complete a brief online survey at three-monthly intervals. The follow up surveys collects information on the number, time, location, reasons for, and results of syphilis tests (including self-tests) and other STI tests at clinics and community sites, and sexual risk behaviors in the past three months. Participants in the two self-testing arms are also asked about the number of self-test kits they used to test their sexual partner(s) or if they gave any kits to someone else to test. At the last follow-up, participants will be asked to get STD (HIV, syphilis, chlamydia, and gonorrhea) screening test in their nearby clinic. The testing fee will be redeemed by an upload of the test results. Participants will be provided with 30 RMB (equal to 4 US Dollars) for their time to complete each follow-up survey.

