**Statistical methods**

***Sample size***

According to our initial pilot study (***Supplementary material***), the proportion of individuals who undertook a syphilis test was 0.36 (95% confidence interval: 0.22 – 0.52) at the one-month follow-up in the control arm. This increased to 0.74 (95% confidence interval: 0.61 – 0.81) in the self-testing arm. On this basis, for the primary outcome with 80% statistical power and type I error probability of 0.05, we conservatively estimate a sample size of 29 per arm (including 20% loss to follow up [25]) for this study. According to our previous experience on using the crowdsourced HIV self-testing intervention in increasing HIV testing among MSM (the proportion was 0.85 [25]), we estimate a sample size of 148 for each arm to achieve 80% power to detect a difference between the crowdsourced lottery incentivized self-testing arm and standard syphilis self-testing arm. Finally, a total of 444 (148 per arm) will be enrolled in this trial.

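### The primary GEE names no baseline covariate; pre-specifying past syphilis and HIV testing, surveyed before allocation, would give a small gain in precision on the lottery contrast at almost no cost

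*Protocol*

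**What the plan says.** The Analysis plan compares arms by "comparing the differences in proportions of men who take syphilis testing during two rounds of follow up by using generalized estimating equation (GEE) model". It gives no link function and no covariate list, and it does not say whether the comparison is adjusted or unadjusted.

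The Surveys section lists the baseline content, including "sexual behaviors, past HIV/syphilis testing and treatment". Under Randomisation and allocation, men reach the research assistant for allocation only after completing that survey, so the information is collected before randomisation. The same section describes blocks of 12 and mentions no stratification factor.

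Eligibility admits only men who report no syphilis test in the last six months. Earlier syphilis testing, and HIV testing at any time, can still vary. On testing history the Background reports that "only 30% of Chinese MSM have ever tested for syphilis".

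The only adjustment the protocol raises is in the Discussion: testing method would be adjusted for if necessary, because of contamination between arms. That variable arises after randomisation.

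**The concern.** Past testing is a natural candidate predictor of testing again. If it predicts uptake, an analysis that leaves it out carries variation that could be explained, and a chance difference between arms in testing history stays in the estimate. The design as described does not balance this factor, and the analysis as described does not use it.

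What is at stake is precision on one contrast. The Sample size section needs 29 per arm for self-testing versus control but 148 per arm for lottery versus standard self-testing, so the second comparison sets the size of the trial and has the least to spare. Naming the covariates before outcomes are seen also removes any later freedom to choose them.

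**Working it through.** **Inputs from the protocol.** The sample size assumes "80% statistical power and type I error probability of 0.05", with "individuals randomized in a 1:1:1 ratio to three study arms". Sidedness is not stated; two-sided is taken here. The pilot control proportion "was 0.36 (95% confidence interval: 0.22 – 0.52) at the one-month follow-up in the control arm"; for standard self-testing the protocol continues: "This increased to 0.74 (95% confidence interval: 0.61 – 0.81) in the self-testing arm". The lottery arm is planned at 0.85. Loss to follow-up is 20%, so 148 enrolled leaves 148 × 0.8 ≈ 118 analysed.

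**The plan's own figures.** With n = (1.96 + 0.842)² × [p1(1 − p1) + p2(1 − p2)] / (p1 − p2)² and (1.96 + 0.842)² = 7.849:

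- 0.36 vs 0.74: 7.849 × 0.4228 / 0.1444 = 22.98, so 23; 23 / 0.8 gives 29. The stated 29 is reproduced.
- 0.74 vs 0.85: 7.849 × 0.3199 / 0.0121 = 207.5, so 208; 208 / 0.8 = 260. The stated 148 is not reproduced (the pooled formula gives 211, or 264 with loss).
- 0.70 vs 0.85: 7.849 × 0.3375 / 0.0225 = 117.7, so 118; 118 / 0.8 gives 148. This matches, but the Study design section gives the pilot results for "both standard self-testing arm (0.74) and lottery incentivized arm (0.70"), so 0.70 is the lottery arm's own pilot rate.

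**Unadjusted power**, pooled two-sided test: Φ{[|p1 − p2|√n − 1.96√(2p̄(1 − p̄))] / √[p1(1 − p1) + p2(1 − p2)]}.

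- Lottery vs standard, 0.74 vs 0.85, p̄ = 0.795, n = 148: (1.338 − 1.119) / 0.566 = 0.388, power 65.1%. At n = 118: (1.195 − 1.119) / 0.566 = 0.134, power 55.3%.
- Self-testing vs control, 0.36 vs 0.74: above 99.9% at either size.

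**What past testing could explain.** Assumptions: a share q of enrolled men ever tested, a gap d in uptake between ever- and never-testers, and overall uptake 0.74. Then R² = q(1 − q)d² / (0.74 × 0.26), and the gain in men per arm is n × [1/(1 − R²) − 1].

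| q | d | R² | men per arm at 148 | at 118 |
|---|---|---|---|---|
| 0.20 | 0.10 | 0.8% | 1.2 | 1.0 |
| 0.20 | 0.20 | 3.3% | 5.1 | 4.1 |
| 0.20 | 0.30 | 7.5% | 12.0 | 9.6 |
| 0.30 | 0.10 | 1.1% | 1.6 | 1.3 |
| 0.30 | 0.20 | 4.4% | 6.8 | 5.4 |
| 0.30 | 0.30 | 9.8% | 16.1 | 12.9 |

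The rows with a 30-point gap are a ceiling. With q = 0.30 and uptake of 0.85 in the lottery arm, ever-testers reach 100% at a gap of 0.15 / 0.70 = 0.21, so a 30-point gap could not hold in both arms of this contrast.

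**Power after adjustment**, 0.74 vs 0.85, replacing n by n/(1 − R²):

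| R² | 148 analysed | 118 analysed |
|---|---|---|
| 0 | 65.1% | 55.3% |
| 0.01 | 65.5% | 55.8% |
| 0.05 | 67.3% | 57.5% |
| 0.06 | 67.8% | 58.0% |
| 0.10 | 69.7% | 59.8% |

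A simulation of a linearly adjusted risk difference with robust standard errors (q = 0.30, d = 0.20) agrees: 64.7% to 67.6% at 148 per arm, and 55.0% to 57.4% at 118. Reaching 80% would need R² of about 1 − 148/211 = 0.30, or 1 − 118/211 = 0.44.

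**Chance imbalance.** With q = 0.30 and 148 per arm, the between-arm difference in ever-tested has standard deviation √(2 × 0.21 / 148) = 5.3 points. A difference of 10 points lies within its 95% range (1.96 × 5.3 = 10.4) and, with a 20-point gap, would move the unadjusted estimate by 0.10 × 0.20 = 2 points, against a planned difference of 11.

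**The case against.** The strongest reply is that nothing here is wrong. A protocol often leaves the covariate list to the statistical analysis plan, which is not at hand, and a GEE takes covariates readily. A reader might infer that the primary analysis is fixed as a raw comparison by arm only; the protocol does not say so. It is silent. That stands, and it is why this is offered as an improvement.

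Randomisation makes the unadjusted difference unbiased, and its standard error already allows for chance imbalance. That stands too: the gain is in precision only.

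The size of the gain is uncertain. A reader might take past testing to be the strongest predictor of uptake, but no document reports any association. The 30% describes Chinese MSM in general; excluding men tested in the last six months plausibly lowers it among those enrolled. The Background also says self-testing may reach men who would not attend a facility, which could weaken the association in the two self-testing arms. The calculations do not credit HIV testing separately, and it probably overlaps with syphilis testing, since the HTC clinics offer both.

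The lottery question is also worded as an additional aim. However, the trial's size is set on it, so its precision matters.

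One technical objection is met by the form of the fix. Adding covariates to a logit GEE and reading off the odds ratio would change the target to a conditional effect and need not shrink its standard error. Standardising back to a marginal risk difference avoids this.

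**Conclusion.** A free improvement, not an error. The primary analysis as written names no baseline covariate, while a plausible prognostic one is surveyed before allocation and the randomisation described does not stratify on it.

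The gain is modest: R² of about 1% to 10%, worth 1 to 16 men per arm at 148 or 1 to 13 at 118, with the upper end unlikely for this contrast. At R² of 0.01 to 0.06, power for lottery versus standard rises by about 0.5 to 3 points; for self-testing versus control there is essentially nothing to gain. These figures assume 20% to 30% ever tested, a gap of 10 to 30 points, a two-sided 0.05 test and a single binary comparison rather than the two-round GEE.

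A reader might infer that adjustment rescues the lottery comparison. It does not. At 0.74 versus 0.85 power is about 65% with 148 analysed and 55% with 118, and no plausible testing-history covariate reaches the R² of 0.30 to 0.44 needed for 80%. The basis of the 148 is a separate matter to settle.

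**What to change.** Add one sentence to the Analysis plan, before outcome data are examined: the primary GEE will use a logit link and include arm, follow-up round, and baseline ever-tested for syphilis (yes/no) and ever-tested for HIV (yes/no); for each contrast the standardised (marginal) risk difference will be reported with a robust standard error, and the unadjusted difference will be given as a supporting analysis.

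The cost is that sentence and a few lines of code, with no new participants or survey questions beyond the testing history already planned. Two small checks belong with it: that the baseline items can be coded as ever/never for each infection, and a rule for unanswered items, since a completed survey does not guarantee that every item was answered. If a statistical analysis plan already names these covariates and this estimand, a cross-reference is enough.

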***Randomisation and allocation***

We will use block randomization with a block size of 12. Computer-generated randomisation codes will be produced and kept by a biostatistician who is not involved in participant enrollment.

Participant enrollment will be carried out online by a research assistant. Interested participants give consent and complete eligibility screening. Eligible participants then complete a baseline survey. Participants who complete the baseline survey are directed to contact the research assistant who is responsible for allocating the participants into one of the three intervention arms based on the randomization code. Participants will be provided with 20 RMB (equal to 3 US Dollars) for their time to complete the baseline survey.

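### The trial-based unit costs include the cost of setting up the study, which overstates the cost per man tested in every arm and, if shared equally, favours self-testing relative to control

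*Protocol*

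**What the plan says.** The costing rule is in the Analysis plan section of the protocol.

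- Scope: "All costs will be identified as start-up costs, fixed costs and variable costs". No step removes costs that exist only because this is a trial.
- Start-up: "Start-up costs are incurred during the process of creating this study (e.g. survey platform coordination".
- Fixed: "Fixed costs are costs that do not change with an increase or decrease in the number of people served during the trial period", with administration and office equipment as examples.
- Variable: "Variable costs are expenses that vary with the number of participants served (e.g. recruitment, supplies, postage fee".
- Calculation: "We will first calculate the total cost for each group, then divided these costs by the number of men tested", and likewise by newly identified cases. The protocol labels this per-arm quotient an incremental unit cost.
- Model: in addition, "we will build a decision tree model using a healthcare provider perspective", which gives the incremental cost per additional person tested and per case identified, with sensitivity analyses.

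Two payments for research participation appear elsewhere. Under Randomisation and allocation: "Participants will be provided with 20 RMB (equal to 3 US Dollars) for their time to complete the baseline survey". Under Surveys: "Participants will be provided with 30 RMB (equal to 4 US Dollars) for their time to complete each follow-up survey". The costing paragraph neither lists nor excludes them.

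**The concern.** The only example of a start-up cost is a research cost. The Surveys section shows the online survey platform hosting the baseline questionnaire, and the Analysis plan retrieves trial data from it. The service itself works differently: under Arms and Interventions kits are ordered through WeChat and posted, and under Data collection tests are confirmed by photograph. A provider offering this service would not pay to set up the trial. The decision tree takes that provider's perspective, but the unit costs in the same paragraph are defined in terms of the study.

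Three things are at stake. Cost-effectiveness is a listed outcome, and the Discussion says the findings will inform the design of a service, so an overstated cost per man tested or per case is a poor planning figure. The overstatement is also uneven, because a cost incurred per randomised man is divided by the proportion tested, which is expected to differ widely between arms. Finally, the per-arm average carries the label incremental, so a reader may take the quantity that study costs distort for the one in which equal costs cancel.

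**Working it through.** The protocol states no cost figure, so there is none to reproduce. The check is algebra, using the protocol's uptake figures.

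**Inputs**
- Proportion tested, p (Sample size; one-month pilot): control 0.36 (95% CI 0.22 to 0.52); standard self-testing 0.74 (0.61 to 0.81).
- Lottery arm, pilot (Study design): 0.70.
- Arm size: 148, randomised 1:1:1. Expected men tested: 148 × 0.36 = 53.3; 148 × 0.74 = 109.5; 148 × 0.70 = 103.6.
- Research-only cost per randomised man, R, and service cost per randomised man, c: not in the protocol, so left as symbols or assumed.

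**Step 1. Inflation in each arm.** The rule gives (c + R)/p. As a service cost it should be c/p. The excess is R/p. For each 1 RMB of R:

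| Arm | 1/p | RMB added per man tested |
|---|---|---|
| Control | 1/0.36 | 2.78 |
| Standard self-testing | 1/0.74 | 1.35 |
| Lottery | 1/0.70 | 1.43 |

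All three are positive, so every unit cost rises.

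**Step 2. Shift in the comparison, with equal R in both arms.** Control minus standard self-testing moves by R(1/0.36 − 1/0.74) = 1.43R in favour of self-testing. Over the pilot limits:
- smallest: 1/0.52 − 1/0.61 = 1.92 − 1.64 = 0.28R
- largest: 1/0.22 − 1/0.81 = 4.55 − 1.23 = 3.31R (from unrounded values)

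The direction does not change within these limits.

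**Step 3. Dependence on the split.** The tilt is zero when R(self-testing)/0.74 = R(control)/0.36, that is when self-testing is charged 0.74/0.36 = 2.06 times control's share per man. Above that it reverses.

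**Step 4. Incremental ratio.** With equal R, [(c1 + R) − (c0 + R)]/(p1 − p0) = (c1 − c0)/(p1 − p0). R cancels.

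**Step 5. Whether a ranking could change.** This uses assumed service costs of 5 RMB (control) and 40 RMB (self-testing) per man, for illustration only:

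| R (RMB) | Control | Self-testing | Incremental ratio |
|---|---|---|---|
| 0 | 5/0.36 = 13.9 | 40/0.74 = 54.1 | 35/0.38 = 92.1 |
| 20 | 25/0.36 = 69.4 | 60/0.74 = 81.1 | 92.1 |
| 50 | 55/0.36 = 152.8 | 90/0.74 = 121.6 | 92.1 |

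The order of the averages reverses where (5 + R)/0.36 = (40 + R)/0.74, so R = (14.4 − 3.7)/0.38 = about 28 RMB. The incremental ratio stays the same throughout.

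The cost per case is overstated in the same way, but the protocol gives no expected case numbers from which to size it.

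**The case against.** A reader might infer that self-testing will look cheaper than it really is. The rule does not do that: each 1 RMB raises self-testing's own unit cost by 1.35 RMB. It gains only relative to control.

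A reader might also infer that the whole cost-effectiveness result is biased. The protocol does not support that either. The comparison of strategies rests on the decision tree, where costs that are equal per man cancel, and nothing says study costs enter it.

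Further objections, and what remains of each:

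- **The split is not stated.** This stands. The relative tilt is conditional on near-equal sharing; the overstatement of the unit costs is not.
- **The platform may serve more than research.** Table 1 has results and photographs going to an unnamed platform. The protocol does not say whether it is the survey platform. If it is, part of its cost would belong to the service. Survey coordination is still research work.
- **Recruitment may be service promotion.** This stands in part. The protocol ties it to participants served, and app banners may be how men would be reached in practice. It cannot simply be classed as research.
- **Pilot uptake may not carry over.** This stands. The figures are for one month, whereas the trial lasts six and asks all arms to be screened at the last follow-up. At an assumed 0.60 and 0.85 the shift would be 1/0.60 − 1/0.85 = 0.49R.
- **No amount in RMB can be fixed.** This stands. Survey payments could total 20 + 30 + 30 = 80 RMB per man, but the costing paragraph does not list them, and the protocol allows for up to 20% loss to follow-up, so not every man would receive them all.
- **This detail belongs in a health-economic plan.** A full list of ledger items could. But the protocol has already fixed a definition and a numerator, and those are what need correcting.

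**Conclusion.** The point holds in a limited form. Followed as written, the rule yields a trial cost per man tested and per case found, so the trial-based unit costs are overstated in every arm as costs of delivering the strategy. That conclusion rests only on the protocol's own definition and example.

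The comparative effect is conditional. It requires research costs shared about equally per randomised man and higher uptake with self-testing. On those terms self-testing gains about 1.43 RMB relative to control for each 1 RMB of research cost per man, with a wide range because the pilot was small (145 men). The total amount cannot be determined, since the protocol gives no costs; the reversal in the worked example shows what could happen, not what is expected.

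The conclusion does not extend to the decision tree's incremental ratio when shared costs are equal per man. The correction is worth making because the averages are labelled incremental and are meant to help plan a service.

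**What to change.** In the Analysis plan section of the protocol:

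1. Define start-up costs as those of setting up the testing service, not of creating the study.
2. Exclude clearly research-only costs from the arm totals: survey platform, survey payments and randomisation.
3. Apply the healthcare provider perspective to both the trial-based unit costs and the decision tree.
4. Show results with and without recruitment costs.
5. Treat the reimbursed screen at the last follow-up alike in numerator and denominator: count both its cost and its tests, or neither. Dropping the cost while keeping the tests would understate unit costs, and could do so unequally between arms.
6. Call the per-arm quotient an average cost. Keep incremental for the between-arm difference in cost divided by the difference in men tested or cases found.

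This takes a rewording of one paragraph and a research-or-service flag in the cost ledger, with no new data or participants. The downside is a small amount of judgement in dividing staff time shared between research and service.

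### The trial-based incremental unit cost is defined as an arm's total cost over that arm's own count, which is an average cost; the same name is then used for a different quantity in the decision tree

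*Protocol*

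**What the plan says.** The economic part of the protocol's Analysis plan opens with its aim: "We will estimate the total and incremental unit costs for each arm". Costs are of three kinds: "All costs will be identified as start-up costs, fixed costs and variable costs". The rule for the unit costs then follows: "We will first calculate the total cost for each group, then divided these costs by the number of men tested" and, continuing the same sentence, the "number of newly identified syphilis cases detected in each study arm to obtain the incremental unit costs".

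The next sentence adds a second analysis, a decision tree from the healthcare provider's perspective. It is meant to "estimate the incremental cost for per additional person tested and case identified for each intervention will be calculated", with sensitivity analyses after it.

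Cost-effectiveness of self-testing is named under Outcomes Measures among the outcomes that follow the primary one. The protocol states no cost total for any arm.

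**The concern.** In the stated rule, numerator and denominator both come from the same arm. That gives what an arm spent per man it tested (or per case it found). An incremental cost answers another question: what each additional man tested costs when one strategy replaces another. It needs a difference in cost over a difference in effect.

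The rule also gives the control arm an incremental cost, although that arm is the reference and has no increment over itself.

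At stake is how the trial-based figure is read. Someone deciding whether to add self-testing to facility-based testing would take a number labelled incremental as the price of the added uptake. The same report would carry the decision tree's figure under the same word, and the two would generally disagree because they measure different things.

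**Working it through.** The protocol has no cost figure to reproduce, so the check is algebra followed by an illustration.

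**1. The two formulas.** Let C be an arm's total cost and E its number tested (or cases), with 1 for the intervention and 0 for the comparator.

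- Stated rule: C1 / E1
- Incremental cost: (C1 − C0) / (E1 − E0)

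**2. When they agree.** Setting them equal and cross-multiplying gives C1·E0 = C0·E1. Apart from trivial cases, this means either C1/E1 = C0/E0 (equal average costs) or C0 = E0 = 0. The second does not fit this trial: control participants are recruited and sent reminders, and the pilot control proportion was not zero.

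**3. What the stated rule mixes.** C1/E1 = (E0/E1)·(C0/E0) + ((E1 − E0)/E1)·(incremental cost). With equal arms and proportions 0.74 and 0.36, the first weight is 0.36/0.74 = 0.49 and the second 0.38/0.74 = 0.51. The stated figure is thus about half the control arm's own average cost and half the increment.

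**4. Inputs for the illustration.** From Sample size: "the proportion of individuals who undertook a syphilis test was 0.36" in the pilot control arm; "This increased to 0.74 (95% confidence interval: 0.61 – 0.81) in the self-testing arm"; and for the lottery arm a planning value from an earlier crowdsourced HIV self-testing intervention, "the proportion was 0.85". Arm size is 148. All cost ratios and totals below are assumptions.

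**5. Cost per man relative to the comparator (comparator = 1).**

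| Comparison | Assumed cost ratio | Stated rule | Incremental |
|---|---|---|---|
| Standard v control | 1.5 | 1.5/0.74 = 2.03 | 0.5/0.38 = 1.32 |
| Standard v control | 3 | 3/0.74 = 4.05 | 2/0.38 = 5.26 |
| Lottery v standard | 1.2 | 1.2/0.85 = 1.41 | 0.2/0.11 = 1.82 |

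For standard v control the error changes sign at a cost ratio of 0.74/0.36 = 2.06. Below that the stated rule is too high, above it too low. For lottery v standard the change comes at 0.85/0.74 = 1.15.

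**6. The stated rule ignores the comparator.** Numbers tested are 148 × 0.36 = 53.28 for control and 148 × 0.74 = 109.52 for standard, a difference of 56.24. Assume a standard-arm total of 6000 arbitrary units. The stated rule gives 6000/109.52 = 54.8 whatever the control arm costs. The increment is:

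- control total 500: 5500/56.24 = 97.8
- control total 2000: 4000/56.24 = 71.1
- control total 5000: 1000/56.24 = 17.8

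At a control total of 2000 the rule would also print 2000/53.28 = 37.5 as the control arm's own incremental cost.

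The algebra applies unchanged to cost per new case. No numbers are given for it, because the protocol states no expected case counts.

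**The case against.** The best defence is that this is a wrong adjective rather than a wrong analysis. The sentence speaks of unit costs for each arm and divides by counts within each arm, so a per-arm average is probably what was meant, and that is a legitimate descriptive figure. The decision tree then plans the quantity that the word incremental properly denotes, for both men tested and cases identified. Nothing in the primary outcome, the sample size or the GEE analysis depends on it, and both ratios can be computed from the same data at any time.

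Most of this stands, and it limits the weight of the point. It does not remove it. The formula and its label are both in the text and do not match. The decision tree is introduced as an addition, so it does not replace the trial-based rule.

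Two stronger readings are tempting and are not supported:

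- **That the plan could not reveal an arm that costs more and achieves less.** The single ratio would hide this, but the plan also estimates each arm's total cost and testing proportion, and those two together would show it. So would the decision tree.
- **That the pilot rates predict this outcome for the lottery arm.** Study design gives 0.70 for lottery and 0.74 for standard, from a pilot of 145 men over all arms. The 0.70 lies inside the pilot interval for the standard arm (0.61 to 0.81), and the trial itself is planned on 0.85 for the lottery arm.

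**Conclusion.** The point holds: the stated rule yields an average cost and calls it incremental. The algebra needs no assumption about this trial's costs. The direction and size of the discrepancy do. Over assumed cost ratios of 1.5 to 3 for standard v control, the stated figure goes from about 54% too high (2.03/1.32) to about 23% too low (4.05/5.26). These figures are illustrative only. The protocol gives no arm costs, the 0.36 is a one-month pilot value where this trial follows men for six months, and the 0.85 comes from another intervention.

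A reader might infer that the economic evaluation has no valid incremental estimate. It does have one, in the decision tree. The defect is confined to one trial-based secondary figure and to the use of one name for two quantities. It is worth correcting because the correction is small and the outcome is meant to inform self-testing policy.

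**What to change.** In the Analysis plan:

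1. Rename arm total cost divided by number tested, and divided by number of new cases, as the average unit cost per arm. Report it for all three arms.
2. Reserve the word incremental for difference in cost over difference in effect between two arms, for standard v control and lottery v standard, for men tested and for new cases, computed from the same trial data.
3. State that this trial-based incremental cost and the decision tree's incremental cost use the same definition, so that any difference between them reflects the model's inputs and not the formula.

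The cost is a few lines of wording. No new data, sample size or change to the primary analysis is needed.
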